## Abstract

**Objective:**

The primary objective of this study is to investigate the effects and biomechanical mechanisms of early gait retraining (GRT) on knee cartilage degeneration following anterior cruciate ligament reconstruction (ACLR).

**Methods:**

This study is a single-blind, parallel-group randomized controlled trial. A total of 60 participants scheduled for primary unilateral ACLR will be recruited and randomly allocated to either the experimental group (conventional rehabilitation plus gait retraining) or the control group (conventional rehabilitation only). Gait retraining will commence at 3 weeks post-surgery, lasting for 6 weeks with a frequency of 2–3 sessions per week, each lasting 15–20 min. Data will be collected at baseline (pre-intervention) and at 3 months, 6 months, 1 year, and 2 years postoperatively. Assessment will include three-dimensional gait analysis, surface electromyography (sEMG), isokinetic muscle strength testing, functional magnetic resonance imaging (fMRI), Y-balance test, single-leg hop test, the International Knee Documentation Committee (IKDC) subjective knee evaluation form, Lysholm knee score, and Tegner activity scale. The primary outcome measure is the peak knee flexion moment during walking. Secondary outcomes include cartilage T1*ρ*/T2 values, muscle activation patterns, and subjective functional scores. A repeated-measures analysis of variance (ANOVA) will be used to evaluate the intervention effects on the outcome measures.

**Results:**

Not applicable.

**Conclusion:**

Early gait retraining using a lower-body positive pressure (anti-gravity) treadmill after ACLR is hypothesized to significantly improve postoperative gait biomechanics. Furthermore, early GRT may optimize standard rehabilitation protocols, potentially preventing or delaying cartilage degeneration. This approach holds clinical significance for restoring normal gait and preventing secondary injuries in individuals with sports-related injuries.

**Clinical Trial Registration:**

https:register.clinicaltrials.gov, identifier NCT06368544

## Introduction

Anterior cruciate ligament (ACL) rupture is a common and severe sports-related knee injury, accounting for approximately 50% of knee sports injuries (1). ACL rupture can lead to joint instability, disrupt the biomechanical homeostasis of the joint, and impair athletic performance (2, 3).

Arthroscopic anterior cruciate ligament reconstruction (ACLR) is currently the preferred clinical treatment for ACL injuries, effectively restoring the structural stability of the knee joint. However, the re-rupture rate after ACLR exceeds 10% (4, 5), and the risk of developing knee osteoarthritis within 10 years post-surgery remains as high as 50% (6). Abnormal gait biomechanics are considered a significant contributing factor to the development of knee osteoarthritis (7–9). Given that walking is a highly repetitive daily activity, long-term abnormal gait patterns can lead to abnormal stress distribution on articular cartilage (10–12). Over time, this may result in secondary lesions such as cartilage damage and meniscal tears, thereby accelerating cartilage degeneration and the onset and progression of osteoarthritis (13–15).

Current standardized postoperative rehabilitation protocols primarily focus on range of motion, muscle strength, balance, coordination, and functional exercises. Previous studies have found that even when patients regain muscle strength and range of motion to levels sufficient for return-to-sport, abnormal gait biomechanics often persist (10, 16, 17). This indicates that current standardized rehabilitation protocols may be insufficient to fully restore normal gait biomechanics after ACLR, and these persistent abnormalities may adversely influence long-term joint health. Therefore, early gait retraining (GRT) is particularly important. GRT involves the use of various biofeedback modalities to target and modify specific aberrant movement patterns, aiming to restore pre-injury gait patterns (18–20). However, no studies have yet explored the impact of early GRT on gait biomechanics after ACLR.

In summary, there is a lack of evidence regarding the effect of early gait retraining on cartilage degeneration after ACLR. Therefore, this study aims to investigate the effects of early postoperative gait retraining on knee cartilage degeneration and its underlying biomechanical mechanisms through a randomized controlled trial, with the goal of providing a theoretical basis for optimizing postoperative rehabilitation protocols after ACLR.

## Methods

### Study design

This study is a prospective randomized controlled trial. The experimental group will undergo gait training in addition to standard rehabilitation, while the control group will receive only standard rehabilitation. Both groups will be assessed at baseline, 3 months, 6 months, 1 year, and 2 years postoperatively (Figure 1).

**Figure 1 F1:**
[figure not shown]
Technical roadmap for the study protocol.

### Participants and recruitment

#### Sample size calculation

The primary outcome measure is the peak knee flexion moment during walking, a key biomechanical indicator of cartilage degeneration (21). A significant difference in this measure will be considered statistically meaningful. Based on preliminary results, the mean peak knee flexion moment before training in ACLR patients is 0.20 BW·BH, with a standard deviation of 0.09. After training, the mean peak knee flexion moment is 0.28 BW·BH, with a standard deviation of 0.11 Nm/kg/m. Using the formula for sample size estimation for two independent samples, $n=\frac{2\sigma^{2}{\left(Z_{\alpha /2}+Z_{\beta }\right)}^{2}}{\delta^{2}}$, with *α* = 0.05 and *β* = 0.2,among $\sigma =\sqrt[{2}]{\frac{\sigma_{1}^{2}+\sigma_{2}^{2}}{2}}$, $\delta =\bar{X_{1}}-\bar{X_{2}}$, the required sample size for each group was calculated to be 25.Accounting for a 20% dropout rate, 30 participants per group will be recruited. The required sample size corresponds to a Cohen's d of 0.8, indicating a large effect size.

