	Stepping exercise	Stand straight, hands at sides, march in place	1	180
	Walking exercise	Walk in front of a mirror, correcting abnormal gait patterns	1	180
Week 4	Straight leg raise	Lift leg 30–60° off the bed, hold until exhaustion	2	1,800
	Knee extension exercise	Place a pillow under the heel, leaving the knee unsupported; relax muscles completely; mild posterior knee discomfort is normal	2	1,800
	Range of motion exercise	Seated beside bed with leg hanging/seated pushing against wall; flex knee to target angle and hold	1	300
	Single-leg stance balance exercise	Stand straight, arms at sides, lift the affected foot and maintain balance	120	5
	High-knee marching exercise	Stand straight, hands at sides, march with high knees	1	180
	Walking exercise	Walk in front of a mirror, correcting abnormal gait patterns	1	300
Week 5	Resisted straight leg raise	With knee extended, lift leg 30–60° off the bed using an elastic band, hold until exhaustion	2	1,800
	Weighted knee extension exercise	Place a pillow under the heel, leaving the knee unsupported; relax muscles completely; a sandbag may be placed above the knee; mild posterior knee discomfort is normal	2	1,800
	Range of motion exercise	Seated, hold the knee to chest; flex to target angle and hold	1	300
	Single-leg stance balance exercise	Stand straight, arms at sides, lift the affected foot and maintain balance	120	5
	Step-up with healthy leg support	Healthy leg supports; affected leg rests on step, slowly perform stepping-up motion	15	3
	Reverse lunge with healthy leg	Stand straight with hands on hips, affected leg flexed at 90°, healthy leg steps back and kneels down	15	5
	High-knee marching exercise	Stand straight, hands at sides, march with high knees	1	300
	Walking exercise	Walk in front of a mirror, correcting abnormal gait patterns	2	300
Week 6	Resisted straight leg raise	With knee extended, lift leg 30–60° off the bed using an elastic band, hold until exhaustion	2	1,800
	Knee extension exercise	Place a pillow under the heel, leaving the knee unsupported; relax muscles completely; a sandbag may be placed above the knee; mild posterior knee discomfort is normal	2	1,800
	Range of motion exercise	Seated, hold the knee to chest; flex to target angle and hold	1	300
	Single-leg stance balance exercise	Stand straight, arms at sides, lift the affected foot and maintain balance	120	5
	Stepping exercise	Stand straight, hands at sides, march in place	1	180

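### The sample size treats a before-to-after-training change (0.20 to 0.28) as the difference between randomised groups, so the stated 80% power leaves essentially no room for improvement in controls

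*Protocol article*

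**What the plan says.** The section "Sample size calculation" of the protocol article names peak knee flexion moment during walking as the primary outcome and takes its planning values from preliminary results. Before training: "the mean peak knee flexion moment before training in ACLR patients is 0.20" (BW·BH), with an SD of 0.09. After training: "After training, the mean peak knee flexion moment is 0.28 BW·BH, with a standard deviation of 0.11 Nm/kg/m". The calculation is introduced by "Using the formula for sample size estimation for two independent samples", "with *α* = 0.05 and *β* = 0.2". Sigma is the root mean square of the two SDs and delta is the difference of the two means. The result is 25 per group, raised to 30 for 20% dropout, with a stated Cohen's d of 0.8.

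The section "Study design" sets the comparison: gait training added to standard rehabilitation against standard rehabilitation alone. The section "Control group" says that both groups follow the same conventional programme. From week 3, Table 2 of that programme includes a walking exercise described as "Walk in front of a mirror, correcting abnormal gait patterns". The protocol reports no control mean, control change or between-group difference for the primary outcome.

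**The concern.** A formula for two independent samples needs the expected difference between experimental and control patients at the time of comparison. A before/after change in treated patients equals that difference only if comparable controls do not change over the same weeks. The change also contains whatever postoperative recovery and standard rehabilitation would have produced anyway, and randomisation subtracts that part. If controls improve by c, the difference available to detect is 0.08 − c.

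This is the only power justification for the primary outcome. If delta does not describe the randomised contrast, then neither the 25 per group, nor the 80% power, nor the d of 0.8 describes the trial. A non-significant result could then be taken as stronger evidence of no effect than the design can give.

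**Working it through.** **Inputs from the protocol (Sample size calculation):** means 0.20 and 0.28; SDs 0.09 and 0.11; two-sided α = 0.05; β = 0.2; 25 per group, 30 recruited; 20% dropout. **Assumed, because the protocol gives no figure:** the control gain c, and the baseline-to-follow-up correlation r.

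**1. Reproduce the plan's figure.**
- σ = √((0.09² + 0.11²)/2) = √0.0101 = 0.1005
- δ = 0.28 − 0.20 = 0.08, so d = 0.08/0.1005 = 0.796
- n = 2 × 0.0101 × (1.960 + 0.8416)²/0.08² = 24.77, rounded up to 25

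The 25 and the d of 0.8 both reproduce, and they do so with δ equal to the full before/after change. The arithmetic is right; the source of δ is the problem.

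**2. Room left for control improvement.** With the plan's formula and 25 per group, the smallest difference with 80% power is 0.1005 × √(2/25) × 2.8016 = 0.0796. This leaves 0.08 − 0.0796 = 0.0004 for any control gain. A two-sample t-test gives 79% power even at zero control gain, because the plan's formula uses the normal approximation.

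**3. Power over an assumed range of control gains** (σ = 0.1005; required n from the plan's formula, before dropout):

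| Control gain c | Difference 0.08 − c | t-test power, 25 per group | Required n per group |
|---|---|---|---|
| 0 | 0.08 | 79% | 25 |
| 0.01 | 0.07 | 68% | 33 |
| 0.02 | 0.06 | 54% | 45 |
| 0.03 | 0.05 | 41% | 64 |
| 0.04 | 0.04 | 28% | 100 |

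**4. What could offset the loss.**
- *All 30 per group retained:* the detectable difference at 80% power is 0.0727 by the plan's formula and 0.0739 by t-test. A control gain of about 0.006 to 0.007 is absorbed.
- *Baseline adjustment at 25 per group:* the SD is multiplied by √(1 − r²). By the plan's formula the detectable difference is 0.069 at r = 0.5 and 0.057 at r = 0.7; by t-test it is 0.070 and 0.058. A control gain of about 0.01 or 0.02 respectively is absorbed. At c = 0.04, t-test power is still only 36% (r = 0.5) or 49% (r = 0.7).

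**5. What the fixed 60 patients can detect.** With 20% dropout, 30 × 0.8 = 24 per group are evaluable. At 80% power the t-test needs d = 0.826, that is 0.826 × 0.1005 = 0.083. With baseline adjustment this is 0.083 × √(1 − 0.5²) = 0.072 at r = 0.5 and 0.083 × √(1 − 0.7²) = 0.059 at r = 0.7.

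**6. Units.** Both means are labelled BW·BH, but the second SD is given "with a standard deviation of 0.11 Nm/kg/m". The two scales differ by a factor of g, so one label must be wrong. If all four numbers are on one scale, d and n do not change.

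**The case against.** The strongest reply is that the power loss is not as stark as the unadjusted figures suggest. Thirty per group are recruited, not 25. The section "Statistical analysis" makes the primary analysis a mixed-effects model, with baseline among the time points, and this may recover power. This stands as a limit on the claim. A reader might infer that 80% power is lost as soon as controls improve at all, whatever the analysis. The protocol does not support that: step 4 shows that full retention or baseline adjustment absorbs a modest gain. But the published calculation uses neither and gives no correlation, so the stated power cannot rest on them.

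A second reply is that control recovery is not shown. This is also fair. The protocol gives no control trajectory for this outcome. The Introduction says that gait abnormalities often persist after standard rehabilitation, and the mirror walking is short and home-based (180 s in week 3, 300 s in week 4). A reader might take recovery in controls as established, or the lower powers as forecasts; neither follows. Equally, incomplete recovery is not absence of recovery, and nothing in the protocol states or justifies a zero control gain.

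Third, the text does not say outright that the same patients were measured before and after training. That is the natural reading, but the point does not depend on it: either way the figures do not contrast a trained group with a control group.

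Finally, the unit mismatch might be read as evidence that the sample size is numerically wrong. It is not, provided that the numbers share one scale.

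**Conclusion.** The concern holds, within limits. The planning difference of 0.08 is a before/after change used as an experimental-minus-control difference, so the stated 80% power does not describe the randomised comparison. On the plan's unadjusted calculation with 25 evaluable per group, that power requires a control gain of essentially zero. For assumed gains of 0.01 to 0.04 it falls to between 68% and 28%.

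These figures rest on the plan's SD of 0.1005, an unadjusted two-sample comparison, and a control gain that the protocol does not supply. They do not show that the trial is underpowered by a known amount; they show that its power is unsupported as stated. The unit inconsistency is a minor separate error.

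**What to change.** In "Sample size calculation":
- State that 0.08 is a before-to-after-training change from preliminary results.
- Restate the planning figure as a between-group difference (experimental change minus control change), and show power over a range of control gains.
- State the difference that 60 patients can detect at 80% power: about 0.083 (d = 0.83) unadjusted with 24 evaluable per group, and about 0.072 (r = 0.5) or 0.059 (r = 0.7) with baseline adjustment, with r declared as an assumption.
- Give all means and SDs in one unit.

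In "Statistical analysis", specify that the primary between-group comparison is adjusted for baseline peak knee flexion moment.

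The cost is rewording and a less favourable power statement. No patients are added.

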#### Inclusion and exclusion criteria

A total of 60 patients scheduled for ACLR will be recruited. After enrollment, participant information will be entered into the RED Cap system, and participants will be randomly assigned to two groups (experimental group, *n* = 30; control group, *n* = 30) using a mixed block randomization method. This is a single-blind randomized controlled trial; participants will not be informed of their group assignment or the intervention details prior to the intervention. Baseline information and data will be collected preoperatively. After the study procedures have been fully explained and understood, written informed consent will be obtained from all participants at the Department of Sports Medicine, Peking University Third Hospital. All data collection and interventions will be conducted at the same department.

Inclusion Criteria: (1) age 18–35 years; (2) diagnosis of ACL rupture confirmed by MRI; (3) first-time unilateral ACL rupture scheduled for reconstruction at our institution; (4) body mass index (BMI) within the normal range of 18.5–23.9 kg/m^2^ (to exclude the confounding effect of obesity on joint loading); (5) time since injury less than 6 months; (6) affected knee has passed the acute phase, with no significant swelling, pain, inflammation, or range of motion limitation, and basic joint mobility is restored.

Exclusion Criteria: (1) history of musculoskeletal injury or surgery on the contralateral lower limb; (2) time since ACL injury 6 months; (3) cartilage injury with Outerbridge grade III or IV; (4) concurrent meniscal tear requiring meniscal repair during ACLR; (5) concomitant severe injury to the posterior cruciate ligament, medial collateral ligament, or lateral collateral ligament; (6) presence of metabolic syndrome (obesity, dyslipidemia, diabetes, etc.), immune system diseases affecting articular cartilage, or severe cardiovascular or cerebrovascular diseases; (7) unwillingness to receive the allocated treatment.

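### Thirty per group does not cover 20% dropout from a required 25: it leaves 24, with 78.7% power by the plan's own formula (a minor shortfall)

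*Protocol article*

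**What the plan says.** All the relevant figures stand in the protocol article, Methods, under Sample size calculation. The primary outcome is the peak knee flexion moment during walking. The planning values are "the mean peak knee flexion moment before training in ACLR patients is 0.20 BW·BH, with a standard deviation of 0.09" and, after training, "the mean peak knee flexion moment is 0.28 BW·BH, with a standard deviation of 0.11 Nm/kg/m". The method is given as "Using the formula for sample size estimation for two independent samples", "with *α* = 0.05 and *β* = 0.2", and the printed formula uses the normal quantile at α/2, so the test is two-sided. The result is that "the required sample size for each group was calculated to be 25". The allowance for losses follows: "Accounting for a 20% dropout rate, 30 participants per group will be recruited". The section ends by describing the effect: "The required sample size corresponds to a Cohen's d of 0.8, indicating a large effect size".

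The next section, Inclusion and exclusion criteria, repeats the recruited number as "experimental group, *n* = 30; control group, *n* = 30", 60 in total. The article gives no other dropout rate, no rule for replacing patients who drop out and no reserve.

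**The concern.** Three stated numbers do not fit together: 25 required, 20% lost, 30 recruited. A dropout rate is a share of those who enter the trial. The step from 25 to 30 instead adds 20% of the number who must remain at the end, which is a smaller allowance. A reader who takes the section at face value will believe that the trial keeps at least 80% power for the primary outcome if one patient in five is lost. On the plan's own figures it does not.

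The allowance matters more here than in a short trial, because follow-up runs to 2 years after surgery with assessments at baseline, 3 months, 6 months, 1 year and 2 years. What is at stake is the accuracy of the sample size statement, not the soundness of the design.

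**Working it through.** **Inputs**, all from Sample size calculation: means 0.20 and 0.28; SDs 0.09 and 0.11; two-sided α = 0.05; β = 0.2; dropout 20%; 30 recruited per group.

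**Step 1. Reproduce the required size.**
- σ² = (0.09² + 0.11²)/2 = (0.0081 + 0.0121)/2 = 0.0101, so σ = 0.1005.
- δ = 0.28 − 0.20 = 0.08, so d = 0.08/0.1005 = 0.796, which the article rounds to 0.8.
- n = 2σ²(Z at α/2 + Z at β)²/δ² = 2 × 0.0101 × (1.960 + 0.842)²/0.0064 = 24.77, rounded up to 25.

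The stated 25 is reproduced. (A one-sided test would give 20, which confirms that the calculation is two-sided.)

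**Step 2. Reproduce the recruited size.**
- 25 × (1 + 0.20) = 30. This is the stated figure.
- 25/(1 − 0.20) = 31.25, rounded up to 32 per group, 64 in total. This is the number that covers 20% dropout.

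Only the first expression gives 30, and rounding cannot bring 31.25 down to 30.

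**Step 3. What 30 per group delivers.**
- With 20% dropout: 30 × 0.80 = 24 per group, one short of 25.
- Largest dropout that still leaves 25: (30 − 25)/30 = 16.7%.

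**Step 4. Power for the plan's own effect, d = 0.796.** By the plan's normal formula, power = Φ(d√(n/2) − 1.960).
- n = 24: Φ(2.758 − 1.960) = Φ(0.798) = 78.7%.
- n = 25: Φ(2.814 − 1.960) = Φ(0.854) = 80.4%.

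For comparison, by the two-sample t-test (noncentral t):

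| n per group | Normal formula | t-test |
|---|---|---|
| 24 | 78.7% | 77.0% |
| 25 | 80.4% | 78.7% |
| 26 | 81.9% | 80.4% |

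With d rounded to 0.80, power at 24 per group is 79.1% by the normal formula and 77.4% by the t-test.

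The loss due to dropout is the difference down a column, 25 to 24: 80.4 − 78.7 = 1.7 points by either method. Against the 80% target the plan's formula falls short by 80 − 78.7 = 1.3 points. The difference between the columns is a separate matter, the choice of normal formula or t-test, and has nothing to do with dropout.

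**The case against.** The strongest reply is that this hardly matters. The unrounded requirement is 24.77, so 24 falls short by 0.77 of a patient per group, and power misses its target by 1.3 points. That is right about the size, and it is why the point is minor. It does not make the sentence correct: in total the plan recruits 60 where its own premises call for 64.

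A second reply is that 24 per group is too pessimistic. The Statistical analysis section plans a mixed-effects model under missing at random, by intention to treat, without deleting anyone. A patient lost before 2 years still contributes earlier visits, and the article does not say by which visit the 20% is lost. If losses come late, more than 24 per group will have 3- or 6-month data. This stands as a mitigation. But the sample size calculation is a plain two-sample comparison with an explicit dropout allowance, and it claims no gain from repeated measures. Nor does the per-protocol sensitivity set gain from partial data, since it requires every follow-up assessment.

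Two stronger readings are tempting, one in each direction.

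- *The power is really 77%, three points short.* That figure combines the dropout slip with a change of method. The article prints a normal formula, and 25 is exactly what that formula yields. Using it is not an error, so the t-test figure is useful context and not the measure of this slip.
- *Adjusting for baseline would recover the lost power.* The documents do not support this. They give no correlation between baseline and follow-up, and they do not state a model with baseline as a covariate; baseline appears as one level of time in the group-by-time analysis. Assuming correlations r of 0.3 to 0.5, equal SDs and the normal formula at 24 per group, covariate adjustment (d/√(1 − r²)) would give about 82% to 89%. A contrast of changes from baseline (d/√(2(1 − r))) would give about 64% to 79%. The sign of the effect on power depends on a choice that the article does not make.

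**Conclusion.** The point holds, and it is minor. The allowance was computed as 25 × 1.2 where 25/0.8 was needed. At the stated dropout of 20%, 30 per group leaves 24, one short of the stated requirement, and power by the plan's own formula is 78.7%, not the 80% or more that β = 0.2 implies.

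This rests on the article's own effect (δ = 0.08, d = 0.796), on dropout of 20% in each group, and on a comparison of patients with data at a single time point, as the calculation assumes. It takes the effect as given. Whether a before-to-after change is a suitable planning value for a difference between groups is a different question, which this check does not settle, so the power figures should not be read as endorsing that input.

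A reader might infer that the trial is underpowered in a way that threatens its conclusions. The figures do not support that: the shortfall is one patient per group and 1.3 points of power, and the mixed model may reduce it.

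**What to change.** Keep 60 patients and restate the dropout sentence in one of two ways:

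1. *Thirty participants per group will be recruited, which allows for a dropout rate of up to 16.7% from the required 25.*
2. *Thirty participants per group will be recruited; with 20% dropout, 24 per group remain, giving about 79% power by the stated formula (about 77% by a two-sample t-test).*

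The first is the simpler, since it corrects the slip without restating power for the assumed effect. If the second is used, the method should be named beside each figure, as shown. Neither version should claim that baseline adjustment restores the power, unless the plan first states such a model and gives a source for the correlation.

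The cost is one sentence and a slightly less favourable figure. No patients are added and neither the design nor the analysis changes. If the sponsor prefers to keep the claim of 20% dropout with 80% power by the stated formula, the matching size is 32 per group, four more patients in total.
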